
### Intervention

Patients in the study will be randomised on a 1:1 ratio to receive either:
Rituximab 1 g on days 1 and 15—study drug250 mL 0.9% sodium chloride on days 1 and 15—placebo.

### Experimental intervention: rituximab

The investigational medicinal product used in the clinical trial is rituximab, 1000 mg intravenously. This product has been approved with the European Commission decision (MA number: EU/1/98/067/002). Patients randomised to receive rituximab therapy will be given treatment at the infusion rates recommended for rheumatoid arthritis patients as per the Newcastle upon Tyne Hospitals NHS Foundation Trust protocol.

### Control intervention: placebo

Patients randomised to receive placebo will receive a control infusion of normal saline. The control infusion will be delivered in a double blinded manner to participants using the same protocol.

### Conditioning

In line with recommendations for the administration of rituximab in other conditions, all patients will receive a conditioning regimen prior to the infusions of study medication on days 1 and 15 to maintain double blinding. The conditioning regimen compromises paracetamol 1 g orally and chlorpheniramine 4 mg orally to be administered 1 h prior to infusion and methylprednisolone 100 mg intravenously to be administered 30 min prior to infusion.

### Concomitant medications

For patients who are on UDCA, the dose will not be changed during the period of study. No other disease-modifying agents should be introduced during the duration of the trial. Therapy aimed at reducing pruritus can be introduced if unavoidable at the discretion of the investigators.

Live vaccines must not be given during the study.

### Randomisation and blinding

Randomisation will be conducted by the Newcastle Clinical Trials Unit (NCTU) web-based system on a 1:1 ratio and random-permuted blocks with random block length. The treatment allocation will be kept blind from the patients, study assessors and investigators until study completion. The randomisation system will generate a treatment number for each participant that links to the corresponding allocated study drug (blinded). A code-break list will be kept in the pharmacy department.

### Study procedures and outcome measures

The schedule of events which includes completion of study questionnaires and collection of mechanistic data is described in figure 1.

**Figure 1 BMJOPEN2015007985F1:**
[figure not shown]
Schedule of events for the RITPBC trial.

### Quality of life and symptom questionnaires

The primary outcome measure is the fatigue domain of the PBC-40. Severity of other symptoms will be assessed in terms of numerical change for the relevant domain of the PBC-40 (itch, cognitive symptoms, social and emotional symptoms). The PROMIS HAQ (Patient-Reported Outcomes Measurement Information System Health Assessment, Questionnaire)^19^ measures the functional and physical ability of the participants (washing, dressing, arising, eating, walking, hygiene, reach, grip and activity). The score is on a 0–100 scale with higher scores indicating worse functional ability. Anxiety and depression will be assessed by the HADS.^20^ Improvement in daytime somnolence will be assessed using the Epworth Sleepiness Scale (ESS).^21^ Vasomotor autonomic symptoms will be assessed using the Orthostatic Grading Scale (OGS).^22^Cognitive function will be assessed with the COGFAIL questionnaire.^23^

### Fatigue diary

Participant-held diaries will be used to gather qualitative information as to symptoms and functional ability. We will use diaries that include both structured (quantitative) and unstructured (qualitative) methods of data collection. The diaries measure fatigue using a scale of 1 to 6 (1—no fatigue and 6—extreme fatigue). Participants will be asked to complete the diaries six times during the study. They will complete the diaries for a period of 1 week at the beginning of each month at baseline, 1, 3, 6, 9 and 12 months. They will return the diaries at the final visit.

### Muscle acidosis

Magnetic resonance data will be acquired at baseline and at 12 weeks using a 3 T Intera Achieva scanner (Philips, Best, the Netherlands) which is equipped with additional specialist hardware to perform phosphorous-31 MRS. The protocol used for acquisition and analysis has been described elsewhere; but in summary, it involves controlled plantar flexion using a purpose-built exercise apparatus developed for operation within the MRI scanner.^14^ Participants will perform 2×180 s bouts of plantar flexion contractions at 25% and then 35% of maximal voluntary contraction, with each bout preceded by 60 s of rest and followed by 390 s of recovery. Phosphorous spectra will be collected at 10 s intervals.

### Anaerobic threshold

Participants will cycle on a stationary ergometer (Corival, Lode, Nederland) between 60 and 70 rpm. The test will be terminated voluntarily by the participant or when they were unable to maintain a pedal frequency of 60 rpm. Expired air will be collected at rest and during exercise using a breathing mask and analysed online using a gas analysis system (MetaLyzer II, CORTEX, Germany). AT will be assessed using the computerised v-slope method and values compared at baseline and 12-week follow-up.

### Physical activity levels

Physical activity will be measured objectively using two activity monitors which will be worn for 7 days at baseline and week 12. The first is a validated multisensor array (SenseWear Pro_3_, Bodymedia Inc) which measures four key metrics: skin temperature, galvanic skin response, heat flux and motion via a three-axis accelerometer. The sensors combined with algorithms calculate the average daily energy expenditure relative to baseline metabolism (metabolic equivalent: MET/day, 1 MET=resting metabolic rate), total energy expenditure (calories per day), active energy expenditure (total calories expended over 3 MET/day), physical activity duration (min over 3METs per day) and average daily number of steps walked. Patterns of sedentary behaviour will be assessed by power law analyses of the lengths of sedentary bouts fitted from raw sedentary data. Outcome measure for study evaluation will be mean number of steps/24 h. Second, the GENEActiv (ActivInsights, Ltd) is a waterproof, lightweight (16 g) triaxial accelerometer. Raw accelerations are collected at a range of ± 8 g with a recording frequency of 40 Hz.

### B-cell biology

Quantification and phenotyping of total B-cell populations and B-cell subsets will be carried out using a FACS-based approach with a well-described protocol utilising markers other than CD20.^24^ Outcome measure will be a chang in individual parameters with therapy. Total and activated B cells in peripheral blood will be evaluated using a direct immune-fluorescence reagent (Fast Immune CD19/CD69/CD45, BD Biosciences). B-cell subsets will be analysed to assess naïve, memory (CD27) and plasma cell (CD38) populations. Finally, activation status of the B-cell populations will be analysed using CD80, CD86 and CD268.

Anti-PDH antibody total and individual isotype levels and antibody functional inhibitory capacity will be studied on day 0 and at the primary end point (12 weeks after therapy). Antibody levels will also be correlated with long-term fatigue status during the secondary follow-up period to 12 months. Anti-PDH levels and isotype patterns will be assessed using a well-established ELISA developed within our research group.^25^ In the analysis phase, impact of rituximab on fatigue in PBC will be correlated with changes in individual autoantibody isotype responses and with PDH-inhibitory capacity of serum.

### Liver biochemistry

We will collect data on the reduction in serum alkaline phosphatase level and attainment of the previously identified positive outcome measure of drop in baseline alkaline phosphatase of >40% or normalisation (Barcelona Criteria).^26^

### Data analysis

#### Sample size calculation

A total sample size of 78 participants (39 per arm) will be recruited and randomised; this includes an assumption of 10% attrition at 12-week follow-up (based on experience in clinical trials in PBC). The primary outcome is the PBC-40 fatigue domain score (range 11–55) after 12 weeks of intervention. The SD of fatigue scores is 8 units (based on the PBC-40 derivation studies utilising >1000 patients^12^), with a correlation of 0.6 between baseline and follow-up time points based on previous studies. The study is powered to detect a mean change in PBC-40 fatigue domain score of 5 units (equating to an average of 0.5 point change per question; a difference in PBC-40 score demonstrated in our population-based studies to be associated with significantly higher levels of social function and which was, therefore, deemed to be clinically significant for the purposes of the study design) with a power of 90% and a 5% significance level. This equates to 35 participants in each group providing data on the primary outcome (PBC-40 fatigue score at 12 weeks): incorporating an assumption of a 10% attrition gives a total of 78. The number of participants lost to follow-up, or withdrawing consent prior to initial treatment is expected to be minimal.

#### Analysis of outcome measures

Analysis will be on the basis of intention to treat.

#### Primary outcome

Differences between intervention and control groups at 12 weeks on PBC-40 fatigue domain scores will be analysed by analysis of covariance (ANCOVA) using baseline scores as covariates. The time course of the comparison between intervention and control groups over the 12-month follow-up period will be assessed using repeated measures analysis of variance.

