#### Secondary outcome

Secondary outcomes, covering comparison of other clinical symptoms and functional capability scales at 12 weeks will also be analysed by ANCOVA using baseline values as covariates. The time course of the comparison between intervention and control groups over the 12-month follow-up period will be assessed using repeated measures analysis of variance.

The analysis of the mechanistic variables will be more descriptive in nature, and will involve comparison of means or proportions between intervention groups, as appropriate, and the use of correlation coefficients to explore the relationship between physiological/immunological measurements and fatigue. For the secondary outcome measures, the variables will be compared at baseline and at 12-week assessment. Physical activity levels will compare mean number of steps per 24 h measured over a 7-day period. AT will be measured during cardiopulmonary exercise testing. MRS will compare the minimum pH seen in the exercise and recovery period, the time required postexercise for pH to return to within 0.01 units of baseline levels (calculated as the sum for each individual of the two bouts to form a total pH recovery time) and the mean ‘area under the curve’ for pH for the 2 exercise episodes which reflects total acid exposure. A change in the number of B cells and B-cell subsets will be reported and also a change in anti-PDH titres. The safety and tolerability of rituximab in PBC will also be reported as a secondary outcome measure.

There are no planned interim analyses for efficacy; however, if the data monitoring and ethics committee (DMEC) requires interim analysis for safety it will be performed. Final analyses will be carried out when all participants have completed the follow-up.

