### Withdrawal of participants

Study drug must be discontinued if:
The participant develops elevated serum ALT/AST four times above the upper limit of normal;The participant decides she/he no longer wishes to continue;Cessation of study drug is recommended by the investigator.

Should a patient withdraw from study drug only, efforts will be made to continue to obtain follow-up data, with the permission of the patient.

Participants who wish to withdraw from study medication will be asked to confirm whether they are still willing to provide the following:
Study specific data at follow-up visits 5–19;End of study data as per visit 19, at the point of withdrawal;Questionnaire data collected as per routine clinical practice at annual follow-up visits.

If participants agree to any of the above, they will be asked to complete a confirmation of withdrawal form to document their decision.

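### The 12-month time course is assigned to repeated measures ANOVA, which in its classical form is complete-case and, as written, has no baseline covariate; a baseline-adjusted mixed model on all observed visits would serve the sustainability aim better

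*Protocol article*

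**What the plan says.** All references are to the protocol article.

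- **Primary outcome.** Fatigue scores at 12 weeks "will be analysed by analysis of covariance (ANCOVA) using baseline scores as covariates". The next sentence says that the comparison of the arms "over the 12-month follow-up period will be assessed using repeated measures analysis of variance". It names no covariate.
- **Secondary outcome.** Symptom and functional scales "at 12 weeks will also be analysed by ANCOVA using baseline values as covariates". The time-course sentence is then repeated: "The time course of the comparison between intervention and control groups over the 12-month follow-up period will be assessed using repeated measures analysis of variance".
- **Analysis of outcome measures.** One general statement: "Analysis will be on the basis of intention to treat".
- **Sample size calculation.** On loss to follow-up, "this includes an assumption of 10% attrition at 12-week follow-up". No figure is given for 12 months.
- **Withdrawal of participants.** "Should a patient withdraw from study drug only, efforts will be made to continue to obtain follow-up data, with the permission of the patient". Those stopping study medication may agree to the remaining study visits, to end-of-study data at the point of withdrawal, or to questionnaires from routine annual visits.

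The text does not say which form of repeated measures ANOVA is meant, how a missed visit is handled, or whether baseline enters as a covariate or as a time level.

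**The concern.** Whether any benefit lasts is a stated aim (Abstract; Study design), and repeated measures ANOVA is the only between-arm method that the article names for it. The method has two weaknesses here.

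**Missed visits.** The classical analysis needs a complete series for each participant. Someone seen at 3, 6 and 9 months but not at 12 contributes nothing. The withdrawal options will produce such partial series, and the article plans to keep collecting them. Completers may also differ from those who leave. If people who are still fatigued leave more often, and at different rates in the two arms, the completers give a biased picture of the 12-month difference.

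**Baseline.** The 12-week comparison gains precision from baseline adjustment, and the sample size relies on that gain. The time-course sentence does not secure it. If baseline is left out, or is used only as a time level, the later comparisons are less precise than the 12-week one for no good reason.

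**Working it through.** **1. The article's own figure.** Inputs from the Sample size calculation: "The SD of fatigue scores is 8 units", baseline to follow-up correlation 0.6, difference 5, power 90%, significance level 5% (taken as two-sided), 10% attrition.

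- Residual SD after baseline adjustment: 8 × √(1 − 0.6²) = 6.4
- n per arm = 2 × [6.4 × (1.960 + 1.282) / 5]² = 34.4, rounded up to 35
- With attrition: 35 / 0.9 = 38.9, so 39 per arm and 78 in total

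This reproduces the stated 35 and 78. The same formula gives 54 per arm for the follow-up score alone (SD 8) and 44 for change from baseline (SD 8 × √(2 × 0.4) = 7.155). The trial's size therefore rests on baseline adjustment.

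**2. What baseline handling is worth at one visit.** With 35 per arm, SE = SD × √(2/35) and power = Φ(5/SE − 1.96).

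| Analysis at one visit | SD | SE | Power |
|---|---|---|---|
| ANCOVA | 6.4 | 1.53 | 90.5% |
| Change from baseline | 7.155 | 1.71 | 83.2% |
| Follow-up score only | 8 | 1.91 | 74.4% |

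If baseline is a time level, the group-by-time contrast of one visit against baseline is the change-score row. If baseline is omitted, the last row applies.

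**3. How many complete cases would remain.** The PBC-40 visit schedule is in a figure that is not shown, and no 12-month attrition is given, so these inputs are assumptions: k = 3 to 5 follow-up visits, intermittent missingness q = 2 to 10% per visit, dropout d = 10 to 20% by 12 months.

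Complete cases = 78 × (1 − d) × (1 − q)^k. Power is for 5 units at one visit with residual SD 6.4, so baseline adjustment is granted.

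| k, q, d | Complete cases | Power |
|---|---|---|
| 3, 2%, 10% | 78 × 0.90 × 0.98³ = 66.1 | 88.8% |
| 4, 5%, 10% | 78 × 0.90 × 0.95⁴ = 57.2 | 84.0% |
| 4, 5%, 20% | 78 × 0.80 × 0.95⁴ = 50.8 | 79.5% |
| 5, 10%, 20% | 78 × 0.80 × 0.90⁵ = 36.8 | 66.0% |

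Some of this loss is due to the missing data and not to the method. The number with an observed 12-month score would be 78 × (1 − d) × (1 − q).

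- Mildest row: 78 × 0.90 × 0.98 = 68.8, or 34.4 per arm. SE = 6.4 × √(2/34.4) = 1.54, power 90%.
- Harshest row: 78 × 0.80 × 0.90 = 56.2, or 28.1 per arm. SE = 6.4 × √(2/28.1) = 1.71, power 83%.

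The part due to deleting incomplete series thus runs from about 1 percentage point (90% to 89%) to about 17 (83% to 66%).

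**4. Bias.** A simulation of 600 trials used 39 per arm, four follow-ups, SD 8, all correlations 0.6 and a true difference of −5 at every follow-up. Dropout depended on the last observed score, with a different dependence in each arm, and about 82% completed. At 12 months the baseline-adjusted complete-case estimate averaged −4.6. A likelihood model on all observed data averaged −5.1. With a Monte Carlo error of about 1.59 / √600 = 0.06, the likelihood result agrees with −5 and the complete-case result does not. The bias of about 0.4 units is roughly a quarter of the estimate's SD of 1.59. The SDs were close (1.59 and 1.55), so in this setting the gain was mainly in bias.

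**The case against.** **The article does not say that incomplete participants are dropped.** This is correct. The label is sometimes used loosely for mixed models that keep partial data, and a full protocol or analysis plan may settle the form. The concern is therefore conditional on the classical form. It is still more than missing detail, because the article names a method, and the ordinary meaning of that name is the complete-case one.

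**A reader might infer that the plan contradicts its intention-to-treat statement.** The documents do not support that. The statement is one general sentence, and seeking data after withdrawal from study drug is consistent with it. What stands is a poor fit if the classical form is used.

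**A reader might infer that the time course ignores baseline, or estimates something different from the ANCOVA.** Neither follows. Silence about a covariate is not exclusion, and with baseline as a time level the interaction contrast does account for it, less efficiently. Under randomisation, adjusted and unadjusted comparisons at the same visit target the same mean difference; adjustment changes precision. Nor does entering baseline as a level dilute the effect of interest. The dilution concerns the main effect of group, whereas a time-course question uses the group-by-time contrasts.

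**The size rests on assumed inputs.** This stands too. The range in complete cases is wide, and the simulated dropout is missing at random, the setting in which a likelihood model does well by construction.

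**The scope is limited.** Muscle acidosis, anaerobic threshold and physical activity are described at baseline and 12 weeks only, so the point barely touches them.

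**Conclusion.** The point holds in conditional form and is worth correcting. If repeated measures ANOVA is run in its classical form, the 12-month comparison would rest on participants with complete series and would lack the baseline adjustment that the neighbouring ANCOVA has.

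On the assumed visit counts and missingness, about 37 to 66 of 78 would remain. Anything from a negligible share to about 17 percentage points of power at one visit would be lost through deletion alone. Separately, handling baseline by change score or not at all would lower power at one visit from 90.5% to 83.2% or 74.4% with 35 per arm. Bias arises only if dropout depends on earlier scores in a way that distorts the comparison between arms; its size cannot be known from the document.

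The 12-week primary ANCOVA, the 35 per arm and the total of 78 are sound on this point and do not change.

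**What to change.** In both the Primary outcome and Secondary outcome sections, for outcomes measured repeatedly to 12 months, replace repeated measures ANOVA with a likelihood-based linear mixed model for repeated measures:

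- data: all observed post-baseline scores of all randomised participants, with no exclusion for a missed visit;
- fixed effects: arm, visit, arm-by-visit, baseline score and baseline-by-visit;
- covariance: unstructured, with a simpler structure named in advance in case the model does not converge;
- report: the arm difference with confidence interval at each visit, including 12 months.

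If a mixed model was what the sponsor meant, one sentence saying so is enough.

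The cost is a change of wording and slightly more analysis work on data already being collected. The model relies on data being missing at random given the observed scores, and the text should say so. Sample size, visits and the 12-week primary analysis stay as they are.

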#### Secondary outcome

Secondary outcomes, covering comparison of other clinical symptoms and functional capability scales at 12 weeks will also be analysed by ANCOVA using baseline values as covariates. The time course of the comparison between intervention and control groups over the 12-month follow-up period will be assessed using repeated measures analysis of variance.

The analysis of the mechanistic variables will be more descriptive in nature, and will involve comparison of means or proportions between intervention groups, as appropriate, and the use of correlation coefficients to explore the relationship between physiological/immunological measurements and fatigue. For the secondary outcome measures, the variables will be compared at baseline and at 12-week assessment. Physical activity levels will compare mean number of steps per 24 h measured over a 7-day period. AT will be measured during cardiopulmonary exercise testing. MRS will compare the minimum pH seen in the exercise and recovery period, the time required postexercise for pH to return to within 0.01 units of baseline levels (calculated as the sum for each individual of the two bouts to form a total pH recovery time) and the mean ‘area under the curve’ for pH for the 2 exercise episodes which reflects total acid exposure. A change in the number of B cells and B-cell subsets will be reported and also a change in anti-PDH titres. The safety and tolerability of rituximab in PBC will also be reported as a secondary outcome measure.

There are no planned interim analyses for efficacy; however, if the data monitoring and ethics committee (DMEC) requires interim analysis for safety it will be performed. Final analyses will be carried out when all participants have completed the follow-up.

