**Trial registration number:**

ISRCTN03978701.

Strengths and limitations of this studyRITPBC is the first randomised controlled trial of a treatment for fatigue in patients with primary biliary cirrhosis (PBC).The trial describes novel mechanistic outcome measures using magnetic resonance spectroscopy (MRS).Novel recruitment strategies utilising the UK-PBC trials platform are described.The main limitation is the responsivity of the primary outcome measure to meaningful improvement in fatigue. Responsivity is one of the 6 psychometric properties of any measure and determines its ability to measure meaningful change in a symptom in response to effective therapy. It is the untested one for the PBC-40 fatigue domain for the obvious reason that there is no therapy able to improve fatigue to allow us to test it. We have mitigated against this by having an objective measure as well (activity) and biomarkers (MRS).

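### The article fixes baseline-adjusted ANCOVA for the symptom scales but a looser comparison for the mechanistic measures (and possibly steps and anaerobic threshold), although their baselines are collected

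*Protocol article*

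**What the plan says.** The section Primary outcome specifies ANCOVA of the 12-week PBC-40 fatigue score with baseline as covariate. The section Secondary outcome extends that model to other clinical symptoms and functional capability scales.

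The same section then treats the mechanistic variables separately. It calls their analysis more descriptive and says that it "will involve comparison of means or proportions between intervention groups, as appropriate", together with correlations against fatigue. No baseline covariate is named. It continues: "For the secondary outcome measures, the variables will be compared at baseline and at 12-week assessment". Steps, anaerobic threshold (AT) and the MRS measures follow directly, while B-cell numbers and anti-PDH titres are to be reported as a change. The section Anaerobic threshold is worded in the same way: "values compared at baseline and 12-week follow-up". Neither of these last two quotes mentions the treatment arms.

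Baselines exist. MRS is acquired at baseline and 12 weeks (Muscle acidosis), AT at the same two points (Anaerobic threshold), activity over 7 days at baseline and week 12 (Physical activity levels), and anti-PDH on day 0 and at 12 weeks (B-cell biology).

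The strengths and limitations box names the untested responsivity of the PBC-40 fatigue domain as the main limitation, and says of it: "We have mitigated against this by having an objective measure as well (activity) and biomarkers (MRS".

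**The concern.** Within one section, the article fixes an efficient baseline-adjusted model for the questionnaires and a less specific, possibly less efficient comparison for the physiological and immunological measures, although a baseline is available for both groups of outcomes. In a trial of about 35 evaluable patients per arm, two things follow if an analyst takes the wording at face value.

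First, comparing week-12 means without the baseline leaves chance baseline imbalance in the estimate and loses precision. Comparing change scores loses less when the correlation is high and more when it is low.

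Second, a comparison of baseline with week 12 that does not name the arms can be carried out as a within-arm test. Such a test mixes any drug effect with retest, learning and seasonal effects, and it is not a randomised contrast.

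The stakes are higher than usual for secondary measures, because the article itself relies on activity and MRS to offset the main weakness of its primary outcome.

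**Working it through.** **Inputs.** From Sample size calculation, all for the PBC-40 fatigue score: "The study is powered to detect a mean change in PBC-40 fatigue domain score of 5 units"; "The SD of fatigue scores is 8 units"; "with a correlation of 0.6 between baseline and follow-up time points based on previous studies"; "with a power of 90% and a 5% significance level"; 35 per arm evaluable; 10% attrition; 78 in total. The article does not state sidedness, so two-sided is assumed. It gives no correlation r for steps, AT, MRS or antibody, so r is varied as an assumption for those.

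**Step 1: reproduce the plan's own figure.** The ANCOVA residual SD is 8 × √(1 − 0.6²) = 8 × 0.8 = 6.4. Then n per arm = 2 × (1.960 + 1.282)² × 6.4² / 5² = 34.4, rounded up to 35. With attrition, 70 / 0.90 = 77.8, rounded up to 78. Both figures match, so the stated sample size already depends on baseline adjustment.

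**Step 2: the same inputs under the three analyses.** With equal SD at both times, the variance factors are 1 for week-12 means, 2(1 − r) for change scores and 1 − r² for ANCOVA. At r = 0.6 (normal approximation):

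| Analysis | Variance factor | SD used | n per arm for 90% | Power at 35 per arm |
|---|---|---|---|---|
| ANCOVA | 0.64 | 6.40 | 35 | 90.5% |
| Change score | 0.80 | 7.16 | 44 | 83.2% |
| Unadjusted week-12 means | 1.00 | 8.00 | 54 | 74.4% |

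This is a benchmark on the fatigue inputs only. It is not a power estimate for any mechanistic outcome.

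**Step 3: range for the outcomes at issue.** The variance of ANCOVA relative to week-12 means is 1 − r². Relative to change scores it is (1 − r²) / [2(1 − r)] = (1 + r)/2. The last two columns take an effect for which ANCOVA has exactly 90% power at 35 per arm.

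| Assumed r | ANCOVA / week-12 means | ANCOVA / change | Power, week-12 means | Power, change |
|---|---|---|---|---|
| 0.3 | 0.91 | 0.65 | 87% | 74% |
| 0.5 | 0.75 | 0.75 | 80% | 80% |
| 0.6 | 0.64 | 0.80 | 74% | 83% |
| 0.7 | 0.51 | 0.85 | 64% | 85% |
| 0.8 | 0.36 | 0.90 | 49% | 87% |

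ANCOVA has the smallest variance throughout. Which alternative loses more depends on r, with the crossover at 0.5.

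**Step 4: what a within-arm test would do.** Suppose both arms shift by 0.3 SD for reasons unrelated to drug, with r = 0.6 and 35 patients in the arm. The standard error of the mean change is √(2 × 0.4 / 35) = 0.151 SD, so the expected z is 0.3 / 0.151 = 1.98. The chance of passing 1.96 is about 51%, with no treatment effect at all. The shift is an assumption; the article gives no figure for it.

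**The case against.** The strongest reply is that the article does not actually commit to a poor analysis. Four inferences are tempting, and the text does not support any of them in full.

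- **That the plan uses raw week-12 means.** The word unadjusted does not appear, ANCOVA is itself a comparison of adjusted means, and the sentence leaves the choice open to what is appropriate. What remains is that a covariate is named for one class of outcome and not for the other, within the same section.
- **That an uncontrolled pre-post analysis is planned.** The mechanistic sentence specifies a comparison between intervention groups. The baseline and week-12 wording can be read as merely giving the time points of that comparison. The within-arm test is a risk of loose wording, not a declared method.
- **That every baseline is ignored.** B-cell and anti-PDH results are reported as change, which uses the baseline. If compared between arms, that is a valid randomised contrast, only less efficient than ANCOVA.
- **That steps and AT are certainly excluded from ANCOVA.** Study design lists them as secondary outcome measures, so they may fall under the opening ANCOVA sentence. Its reference to symptoms and scales points the other way but does not settle it.

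It is also fair to say that the mechanistic analysis is declared descriptive, that an analysis plan not shown may give the model, and that the 0.6 correlation belongs to the fatigue score alone. An unadjusted randomised comparison is unbiased on average, so the issue there is precision.

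These points limit the finding but do not remove it. The point does not rest on missing detail: the article assigns the two classes different analyses, and its time-point wording omits the arms. Descriptive status also sits uneasily with using activity and MRS to back up the primary outcome.

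**Conclusion.** The point holds in a limited form. For outcomes with a collected baseline, the article names a group comparison without a covariate, or a reported change, where it could name the ANCOVA that it already uses for the questionnaires. In two places it also describes a comparison over time without mentioning the arms.

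The size cannot be fixed from the document. It rests on the assumed r of 0.3 to 0.8, on equal SD at the two time points, and on which analysis would really be used. Against change scores the disadvantage is modest at high correlation (ANCOVA has 90% of the variance at r = 0.8). Against unadjusted means it is small at low correlation (91% at r = 0.3) and large at high correlation (36% at r = 0.8).

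The primary analysis and the sample size already use baseline adjustment and are not affected. This is a worthwhile correction to secondary and mechanistic analyses, not a threat to the main result.

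**What to change.** State that continuous steps, AT, MRS and antibody outcomes are compared between arms at week 12 by ANCOVA, with each outcome's own baseline as covariate, and that the between-arm difference is reported with a 95% CI. Reword the baseline and week-12 sentences in Secondary outcome and Anaerobic threshold so that the arms are named.

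Choose a transformation or rank-based method measure by measure, not one rule for all. A blanket log would fail for B-cell counts, which may reach zero under a B-cell depleting drug. It would also not deal with pH recovery times that are cut off because recovery is observed for only 390 s after each bout.

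Present within-arm changes from baseline to week 12 as description, without tests.

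The cost is a change of analysis wording, best settled before unblinding. No new data, visits or patients are needed.
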